## Abstract

**Introduction:**

Some people, who have common mental health disorders such as depression and anxiety, also have some psychotic experiences. These individuals may experience a treatment gap: their symptoms neither reach the increasingly high threshold for secondary care, nor do they receive full benefit from current interventions offered by the Improving Access to Psychological Therapies (IAPT) programme. The result may be poorer clinical and functional outcomes. A new talking therapy could potentially benefit this group. Informed by principles of coproduction, this study will seek the views of service users and staff to inform the design and development of such a therapy.

**Methods and analysis:**

Semistructured interviews will be conducted with IAPT service users, therapists and managers based in three different geographical areas in England. Our sample will include (1) approximately 15 service users who will be receiving therapy or will have completed therapy at the time of recruitment, (2) approximately 15 service users who initiated treatment but withdrew, (3) approximately 15 therapists each with at least 4-month experience in a step-3 IAPT setting and (4) three IAPT managers. Data analysis will be based on the constant comparative method.

**Ethics and dissemination:**

The study has been approved by the London Harrow Research Ethics Committee (reference: 18/LO/0642), and all National Health Service Trusts have granted permissions to conduct the study. Findings will be published in peer-reviewed academic journals, and presented at academic conferences. We will also produce a ‘digest’ summary of the findings, which will be accessible, visual and freely available.

Strengths and limitations of this studyThis study will address the needs of a currently underserved group: people with a common mental disorder who also have psychotic experiences.The multiperspective approach will provide insights into limitations of current treatments and inform the development of a new, more targeted talking therapy.The study will not include real-time observations of therapeutic encounters which might generate more insight into how service users and therapists interact and coconstruct care.

## Introduction

Some people, who have common mental health disorders such as depression and anxiety, also have some psychotic experiences, such as attenuated paranoia or voice hallucinations.^1–7^ These experiences are likely indicators of severity of mental distress and associated trauma. For example, people with psychotic experiences are at least seven times less likely to reach remission of depressive symptoms, are at increased risk of self-harm^1–5^ and show poorer response to standard psychological treatments for depression and anxiety, even in combination with pharmacotherapy.^8–10^ Despite the clinical relevance of psychotic experiences in anxiety and depression, and the evidence that psychosis, depression and anxiety may share common aetiologies,^11–18^ current psychiatric diagnostic classifications do not adequately acknowledge the presence of psychotic experiences in common mental disorders. This has important consequences, not least because psychiatric diagnostic classification systems are used to configure how mental health services are organised in England, which in turn impacts on how those services are accessed and used.

The Improving Access to Psychological Therapies (IAPT) programme in England is particularly important for addressing common mental disorders. IAPT provides steps 2 and 3 in the National Institute for Health and Care Excellence four-step approach to the treatment of common mental disorders.^19^ Cognitive–behavioural therapy (CBT) is the predominant, but not the only approach adopted by these services, particularly for depression where there is a wider range of recommended treatments (counselling, couples therapy, interpersonal therapy, brief psychodynamic therapy and CBT).^20^ At step 2, psychological well-being practitioners provide referral advice and CBT treatments to people with persistent subthreshold symptoms and mild to moderate common mental disorders. At step 3, high intensity therapists treat people with moderate to severe common mental health disorders and those who do not show sufficient improvement in response to initial interventions at step 2.

All IAPT services routinely collect patient-reported outcomes measures. The 9-item Patient Health Questionnaire (PHQ-9)^21^ and 7-item Generalised Anxiety Disorder (GAD-7)^22^ measures for depression and anxiety, respectively, used at baseline and following each treatment session allows the calculation of ‘reliable recovery’. This is judged to occur if a person scores below the clinical threshold on PHQ-9 (score ≤10) and GAD-7 (score ≤8) post-treatment, and also shows a significant improvement in their condition.^23^ Psychotic experiences are not currently routinely measured in IAPT services, although a recent study has shown that approximately 30% of people treated in IAPT services had psychotic experiences.^24^ Reliable recovery remains at around 48% of the IAPT population as a whole,^23^ but those with a common mental disorder and psychotic experiences may be much less likely to recover,^24^ again suggesting greater severity of illness.

People with a common mental disorder including psychotic experiences thus may face a substantial gap in services; their symptoms do not reach the increasingly high threshold for secondary care^25^ but the standard CBTs used in IAPT do not target psychotic experiences nor the trauma histories with which they are often associated.^8–10^ Focusing on mood disturbance alone, as IAPT services currently do, is likely to result in psychotic experiences being left untreated, and could contribute to poorer clinical and functional outcomes.

Just as the condition itself (common mental disorder with psychotic experiences) is scattered across different chapters of Diagnostic and Statistical Manual of Mental Disorders (DSM-5),^26^ evidence-based psychological treatments are scattered between different service settings that are inadequate to assess or treat the condition in a holistic manner. By reconfiguring and assembling such treatments into a new talking therapy for use in the low stigma setting of IAPT services, the prospects of recovery might be greatly improved. To maximise effectiveness and applicability within the IAPT setting, the new talking therapy should be grounded in a thorough understanding of the priorities and views of IAPT service users, therapists and managers, and should be based on principles of coproduction.

### Coproduction: a collaborative approach to healthcare improvement

Based on relationships of reciprocity and mutuality among citizens, service users and clinicians, coproduction seeks to improve health and support the development of user-led, people-centred health services. Viewing users as active agents and employing an asset-based model, in which narratives and experiences of illness, services and treatment contribute to health research, service improvement and knowledge, it is firmly rooted in the principle that bringing together clinical, lay and biomedical knowledge allows new forms of values, knowledge and social relations to emerge. Coproduction frameworks are increasingly used as a means to guide the reform and improvement of mental health services,^27–32^ with the National Health Service (NHS) England Five Year Forward View for Mental Health specifying that coproduction between managers, clinicians and service users should be at the heart of service design. For example, Memon *et al*
33 interviewed 26 adults from black and minority ethnic backgrounds to examine perceived barriers to accessing mental health services, with the aim of informing the development of effective services to improve equity in healthcare. Similarly, Bee *et al*
34 explored the views of professionals on how to improve service users and carer involvement in mental healthcare planning. Accordingly, the design and execution of our investigation will be based on the involvement of key stakeholders to facilitate the identification and in-depth examination of key priorities for improvement.

### The study

The proposed study is part of a wider research programme grant led by the Department of Psychiatry, University of Cambridge. As part of this wider research programme, the proposed study is expected to inform the design and development of a new talking therapy that aims to improve the prospects of recovery for people with a common mental disorder including psychotic experiences who are attending IAPT services.

### Aims and objectives

The study is located within the interpretivist tradition of scientific enquiry exploring individuals’ subjective experiences and meaning-making processes of social reality.^35^ The focus of qualitative methodologies on the meaning and meaning-making processes of social phenomena and events^36^ is consistent with the aims of our proposed study, which are to:Produce an in-depth account of both the challenges and positive experiences reported by IAPT users who have a common mental disorder that includes psychotic experiences in receiving care from current step-3 IAPT services, including their views on their therapist(s), the talking therapy they were offered, how it was implemented, how far they saw it as effective in addressing their mental health needs, and their ideas, values and priorities for the development of a new talking treatment and for improving therapists’ skills in treating service users with a common mental disorder including psychotic experiences.Produce an in-depth account of both the challenges and positive experiences of IAPT therapists in delivering care for IAPT users with a common mental disorder including psychotic experiences, including therapists’ understanding of the term ‘common mental disorder including psychotic experiences’, and their views on the value, role and effectiveness of the talking therapy they currently use and of clinical skills in addressing such manifestations, as well as their ideas, values and priorities for the development of a new talking treatment and for improving therapists’ skills in treating service users with such experiences.Produce an in-depth account of IAPT managers’ experiences in delivering and supporting the delivery of care for IAPT users with a common mental disorder including psychotic experiences, including managers’ views on the current pathways of care and their effectiveness, their impact on meeting performance and recovery targets, as well as managers’ ideas, values and priorities for the development of a new talking treatment and for improving therapists’ skills in treating service users with common mental disorders including psychotic experiences.

## Methods and analysis

### Study design

The study will conduct semistructured interviews to explore the views of IAPT service users and staff.

### Recruitment, sampling and selection of service users for interview

The proposed study will take place in three IAPT provider sites based in the East and Southeast of England. We aim to recruit up to approximately 30 service users who meet our criteria for a common mental disorder including psychotic experiences from across the participating IAPT provider sites (see tables 1 and 2). Around half (n=15) will be in therapy (at least four sessions) or will have completed therapy at the time of recruitment; the other half will have initiated treatment but withdrawn. We believe that this number will be sufficient to achieve theoretical saturation,^37^ whereby no further themes emerge as additional participants are included, but we will monitor this carefully. We will collect demographic data of service users, such as age, gender and ethnicity. We will use quota sampling to ensure diversity of gender and ethnicity, by matching the proportion of subgroups to the population (eg, roughly half of the sample will be female participants). We will then choose potential participants by adhering to the subgroup population proportion.

**Table 1 T1:** Inclusion and exclusion criteria for people who are in therapy or have completed their therapy

Inclusion	Exclusion
Male or female 18 years of age or over PHQ-9 score ≥10 and/or GAD-7 score ≥8 (at any point during the therapy) CAPE-P15 scores ≥1.47 for frequency and ≥1.47 for distress Expressed an interest in participating in research either via the CAPE-P15 or IAPT registration form Have completed or attended at least four therapy sessions at the time of recruitment	PHQ-9 score ≤10 and/or GAD-7 score ≤8 CAPE-P15 scores ≤1.47 for frequency and ≤1.47 for distress Have not expressed an interest in participating in research neither in CAPE-P15 not IAPT registration form Have attended fewer than four therapy sessions at the time of recruitment

CAPE-P15, Community Assessment of Psychic Experiences-Positive 15 items; GAD-7, 7-item Generalised Anxiety Disorder; IAPT, Improving Access to Psychological Therapies; PHQ-9, 9-item Patient Health Questionnaire.

**Table 2 T2:** Inclusion and exclusion criteria for people who initiated treatment but withdrawn

Inclusion	Exclusion
Male or female 18 years of age or over PHQ-9 score ≥10 and/or GAD-7 score ≥8 (at any point during the therapy) CAPE-P15 scores ≥1.47 for frequency and ≥1.47 for distress Expressed an interest in participating in research either via the CAPE-P15 or IAPT registration form Initiated treatment but withdrawn	PHQ-9 score ≤10 and/or GAD-7 score ≤8 CAPE-P15 scores ≤1.47 for frequency and ≤1.47 for distress Have not expressed an interest in participating in research neither in CAPE-P15 nor IAPT registration form

CAPE-P15, Community Assessment of Psychic Experiences-Positive 15 items; GAD-7, 7-item Generalised Anxiety Disorder; IAPT, Improving Access to Psychological Therapies; PHQ-9, 9-item Patient Health Questionnaire.

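### In Tables 1 and 2 the PHQ-9/GAD-7 exclusion row is not the complement of the inclusion row: read literally, it rejects users whom the inclusion row admits

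*Protocol article*

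**What the plan says.** The section on recruitment, sampling and selection of service users sets eligibility in two tables. Table 1 covers people in therapy or with therapy completed; Table 2 covers people who started and withdrew. Both tables carry the same PHQ-9/GAD-7 rows:

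- Inclusion: "PHQ-9 score ≥10 and/or GAD-7 score ≥8 (at any point during the therapy").
- Exclusion: "PHQ-9 score ≤10 and/or GAD-7 score ≤8". No time point is attached.

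Four other places bear on how these rows work:

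- The Introduction says that the two measures are "used at baseline and following each treatment session", so each user has a series of scores.
- The Introduction describes reliable recovery as a person who "scores below the clinical threshold on PHQ-9 (score ≤10) and GAD-7 (score ≤8) post-treatment" and also improves significantly. These are the same values as in the exclusion row.
- The recruitment section makes completers part of one target group: "Around half (n=15) will be in therapy (at least four sessions) or will have completed therapy at the time of recruitment".
- The Introduction describes the population in these terms: "Some people, who have common mental health disorders such as depression and anxiety, also have some psychotic experiences". Nothing requires a user to be raised on both scales.

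The Sampling section selects cases on the CAPE-P15 alone. No section says which PHQ-9/GAD-7 row prevails when both apply.

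**The concern.** An exclusion row that only mirrors an inclusion row should be its exact negation. The negation of 'PHQ-9 at least 10 or GAD-7 at least 8, at some point' is 'PHQ-9 below 10 and GAD-7 below 8, at every point'. The printed row differs from this in three ways:

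1. **Connective.** It keeps 'and/or' where negation turns 'or' into 'and'.
2. **Boundary.** It uses ≤ where negation of ≥ gives <, so 10 and 8 lie on both sides.
3. **Time.** It drops the qualifier that the inclusion row carries. In Table 1 the criterion on number of sessions is tied to the time of recruitment in both columns; the score exclusion is tied to nothing.

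The consequence is that the same person can be both eligible and ineligible. The first aim asks for positive experiences as well as challenges, from users with a common mental disorder that includes psychotic experiences. Users with depression only, users with anxiety only, and completers who did well all belong to that population, and the printed row could remove some or all of them. Monitoring saturation would not reveal the loss of a group that was never approached.

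**Working it through.** The plan gives no figure to reproduce here. The check is logical, supported by a count of score pairs.

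**Inputs.** The cut-points and connectives come from Tables 1 and 2, and the recovery values from the Introduction. The documents do not give the scale ranges. I assume PHQ-9 0-27 (28 values) and GAD-7 0-21 (22 values), and repeat the count with 0-20 and 0-15.

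**Rules at a single time point**

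- Include: P ≥10 or G ≥8.
- Exclude, literal 'or': P ≤10 or G ≤8.
- Exclude, lenient 'and': P ≤10 and G ≤8.
- True complement of inclusion: P <10 and G <8.

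**Count, ranges 0-27 and 0-21**

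- All pairs: 28 × 22 = 616.
- Failing inclusion (P 0-9, G 0-7): 10 × 8 = 80, so 616 − 80 = 536 meet inclusion.
- Escaping the literal exclusion (P 11-27, G 9-21): 17 × 13 = 221, so 536 − 221 = 315 meet both rows (315/536 = 59%).
- Meeting the lenient exclusion (P 0-10, G 0-8): 11 × 9 = 99, so 99 − 80 = 19 meet both rows.

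| Included pairs | Number | Also excluded, 'or' | Also excluded, 'and' |
|---|---|---|---|
| Raised on PHQ-9 only | 18 × 8 = 144 | 144 | 8 |
| Raised on GAD-7 only | 10 × 14 = 140 | 140 | 10 |
| Raised on both | 18 × 14 = 252 | 252 − 221 = 31 | 1 |
| Total | 536 | 315 | 19 |

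The 31 are the boundary pairs, with PHQ-9 exactly 10 or GAD-7 exactly 8. With ranges 0-20 and 0-15 the literal overlap is 186 of 256, and every single-scale pair is again excluded (88 of 88 and 80 of 80). The logical result does not depend on the assumed ranges. With the true complement the overlap is 0.

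**Time.** The faults depend on different readings.

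- *User raised on one scale only throughout.* Under 'or', the other scale is at or below its cut-point at every assessment. The user is excluded whichever assessment is used. This fault depends on the connective, not on timing.
- *Completer who met inclusion earlier and then recovered.* The end-of-therapy scores satisfy P ≤10 and G ≤8, so all 99 such pairs are excluded under either connective. This fault arises only if the row is applied to current, end-of-therapy or any recorded scores. It does not arise if the row must hold at every assessment and the user was earlier above both cut-points, or was earlier above at least one and the connective is 'and'.

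**The case against.** The strongest reply is that the intent is plain. In both tables the exclusion column restates the inclusion column in the negative, so a sensible screener would read this row as the complement. The recruitment text selects users positively, by CAPE-P15 score, expressed interest and quota, and never describes the PHQ-9/GAD-7 exclusion as a separate screen. The only time anchor printed, in the inclusion row, keeps recovered completers, and Table 1 names completers as a target. The Introduction's recovery definition is background and sets no eligibility rule. On this view the fault is one of wording.

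Much of that stands: this is most likely a drafting error. But the complement is reached only by changing the connective, changing the cut-points and supplying a time point, and no section does any of these. A row headed as an exclusion is normally applied as one.

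A reader might infer more than the documents support:

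- *That 59% of eligible users would be lost.* The count weights every score pair equally, and the documents give no joint distribution of scores in this group.
- *That every recovered completer is excluded.* That needs the row to be applied to later scores, which the text neither says nor rules out.
- *That the sample would consist mainly of comorbid non-responders and overstate the case for a new therapy.* Anyone passing the literal row is indeed above both cut-points. How far that changes the sample depends on how many eligible users are raised on one scale only, which is not given. Remaining above the cut-points is also not non-response: a user whose PHQ-9 falls from 24 to 12 has improved and is not excluded on that score. About half the users will have withdrawn, and the other half includes people still in therapy. The study gathers views to inform a therapy's design; it does not test whether one is needed.
- *That sites would screen differently.* The research team chooses whom to approach, so the text gives little ground for this.

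**Conclusion.** The contradiction is certain and stands on the face of both tables. As printed, the exclusion row rejects all users raised on only one scale, whom the inclusion row admits, and places scores of exactly 10 or 8 on both sides. The first of these rests on reading 'and/or' as an inclusive or; under 'and' only boundary scores conflict at a single time point. The loss of recovered completers is conditional on applying the untimed row to current or later scores.

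The effect on the interviewed sample cannot be sized from the documents, and nothing shows that anyone was turned away on this row. The Limitations section acknowledges that recruitment and sampling may influence the findings, but not for this reason. The point is a wrongly stated eligibility rule that would select the wrong sample if followed. It should be corrected because the rule cannot be audited as written; no bias has been shown.

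**What to change.** In Tables 1 and 2, either delete the PHQ-9/GAD-7 exclusion row, since the inclusion row already decides the matter, or replace it with the exact complement: PHQ-9 <10 and GAD-7 <8 at every assessment during therapy.

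The Study status section says that data collection began in June 2018 and should last 7 months. The team should therefore confirm that no user was turned away on the printed row and, if anyone was, review those cases against the corrected rule.

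The cost is one row in each table and a check of screening decisions already made. The target of about 30 service users does not change.

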### Sampling

The research team has liaised and worked collaboratively with IAPT managers and therapists from the participating IAPT provider sites to agree on the most convenient procedures for service user recruitment, which will minimise the effort required from IAPT staff while maximising the likelihood of reaching the above recruitment targets. The proposed study will focus on adult female and male service users, as people below 18 years old have different mental healthcare structures and service delivery within IAPT and are not the focus of our study. Non-English speakers will be included.

We will employ a two-step method to help us ensure that we identify, approach and recruit the right sample while reducing the risk of causing unnecessary distress to service users. First, in addition to assessment measures currently used for depression (PHQ-9) and anxiety (GAD-7), the participating IAPT provider sites administer the shortened version of the Community Assessment of Psychic Experiences questionnaire Positive-15 items (CAPE-P15)^38^ as part of a service evaluation to identify the prevalence and impact of psychotic experiences in their current caseloads. All service users attending step-3 IAPT services are offered the opportunity to complete the self-reported CAPE-P15 questionnaire once during the course of their treatment.

The CAPE-P15 is a 15-item, self-report measure of experiences that are similar to positive psychotic symptoms, such as perceptual abnormalities, persecutory ideation and bizarre experiences. It measures the frequency (ranging from 1-never to 4-nearly always) and level of distress (ranging from 1-not distressed to 4-very distressed) that each psychotic experience causes to the individual. To account for non-response to any items, scores are weighted for the number of valid answers. The weighted score is the sum score divided by the amount of items completed (ie, the mean of completed items). Higher scores indicate a higher frequency of psychotic experiences and an increased level of distress in relation to these experiences. A cut-off point ≥1.47 for frequency and a cut-off point of ≥1.47 for distress has been useful for detecting people who have psychotic experiences.^39^ Service users who have scored in ≥1.47 for both frequency and distress in CAPE-P15 will be considered as cases, and therefore, eligible to participate in our study.

Second, at the end of the CAPE-P15, we have added a query where we ask service users to indicate, by ticking a box, whether they are interested in taking part in the proposed study and discuss their experiences of using step-3 IAPT services. From among those service users with scores of ≥1.47 for both frequency and distress on CAPE-P15, we will approach a proportion of those service users (following the quota sampling method) who indicated in the CAPE-P15 questionnaire that they would like to participate in the proposed study. We will also include service users who have indicated in their IAPT registration form that they want to take part in research projects. To ensure confidentiality, we will use service users’ IAPT numbers (unique identification numbers, similar to NHS numbers, but exclusively used within IAPT services). This approach will allow us to approach the right sample and minimise the risk of unduly stressing potential participants, as well as ensure that service users’ data and confidential information are protected.

